**Fig 1 pone.0338801.g001:**
[figure not shown]
Conceptual framework.

## Methods and analysis

### Study design

This study employs an observational, age-matched case-control design, comparing children with ASD as cases with TD children as healthy controls. The case-control approach allows the identification of potential links and exposures related to risk factors for ASD. This design contributes to the growing body of evidence exploring the risk factors for ASD in children [30]. This study is currently in progress, with data collection and analysis expected to be completed in June 2026.

### Study Population and setting

Male children between 4–10 years old who comply with the protocol definition and inclusion criteria will be enrolled as participants. Cases are defined as male children diagnosed with ASD and receiving under follow-up care at the Paediatric Clinic at HTJ. Controls are defined as age-matched, TD healthy male children from daycare centres near IMU Healthcare and TABIKA KEMAS in Seremban. These locations were selected based on convenience sampling. Cases and controls are matched within using an age range of ±6 months.

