### Objectives

This study primarily aims to understand the role of oral and gut microbiota in the molecular mechanisms underlying the aetiology of ASD among children in Malaysia. Specifically, this study aims to determine whether there is an association between the oral and gut microbiota and socio-demographic factors, nutritional status, and autism severity among children with ASD compared to TD healthy children. Additionally, this study also measures additional independent variables to determine the associations between oral and gut microbiota and gastrointestinal symptoms, eating behaviour, behavioural profiles and sleep quality.

The hypothesized relationships between gut microbiota, nutritional status, dietary intake, and ASD severity are illustrated in Fig 1.

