### Eligibility criteria and screening procedures

The ASD group is male children aged 4–10 years diagnosed with ASD according to the Diagnostic and Statistical Manual of Mental Disorders, Fifth Edition (DSM-5) criteria, based on the evaluations performed by the child development team [35]. ASD diagnosis is confirmed by a developmental paediatrician through evaluations of medical history and clinical symptoms. The inclusion criteria for the ASD group are as stated: (1) male children aged 4–10 years who meet the DSM-5 criteria for ASD; and (2) whose parents or legal authorized representative (LAR) is willing to provide informed consent on their behalf. The exclusion criteria for the ASD group are as stated: (1) children below age of 4 years and above 10 years old; or (2) children who do not meet the case definition; or (3) children who have are on medications such as Ritalin and antipsychotics, anti-inflammatory, antioxidant drugs, or antibiotics in the three months prior to sample collection.

The TD group included healthy male children aged 4–10 years, with no history of early developmental delay, learning difficulties, or any other neurological or psychiatric conditions. Participants must not have been on medications such as Ritalin, antipsychotics, anti-inflammatory, antioxidant drugs or antibiotics in the three months prior to sample collection. Children with first degree relatives diagnosed with neurological, psychiatric, or neurodevelopmental disorders are excluded. TD children are defined as those achieving age-appropriate developmental milestones across gross motor, fine motor, language, cognitive, social-emotional and behavioural development. In Malaysia, routine health examinations monitor infant and child growth and developmental progress. Children were classified as TD if parents reported no developmental concerns from healthcare providers and no learning difficulties noted by schoolteachers.

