### Recruitment

Children with ASD are identified by the developmental paediatrician at HTJ, Seremban, whereas TD healthy children are recruited from daycare centres or TABIKA KEMAS in Seremban. Data collection is performed by a trained graduate research assistant, acting as the research enumerator commenced on 24^th^ August 2024. Parents or legal guardians are given the study information sheet and to obtain their signed consent forms by the research enumerator. Participant recruitment and data collection are estimated to be completed in June 2026. Fig 2 below illustrated the study protocol workflow.

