### Data collection sheet

This sheet contains two sections as follows: (1) Information on participant and family demographics (child’s gender, age, gestational age, birth weight, parent’s age, ethnicity, occupation, education level, and household income); and (2) ASD medical history (age of first presentation, first presenting complaint, family history of ASD or other neurodevelopmental disorders (NDDs)) and other relevant medical conditions, if applicable.

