### Nutritional status and dietary assessment

A Subjective Global Nutrition Assessment (SGNA) will be utilised to determine the nutritional status of the children [49]. SGNA evaluates nutritional status in two main categories: Nutrition Focused Medical History (NFMH) and Physical Exam (PE). NFMH includes evaluating the appropriateness of current height and weight for age, changes in body weight, dietary adequacy, gastrointestinal symptoms, functional capacity, and metabolic aspects of disease. PE evaluates subcutaneous fat loss, muscle wasting, and nutrition-related oedema. The combined NFMH and PE evaluation will generate an overall SGNA ranking of normal/well-nourished, moderately malnourished, severely malnourished [49].

Dietary intake of the children will be obtained through parental interviews, using 3-day dietary recalls (two weekdays and one weekend day). To assist with the food intake portion size estimation, pictures of household measuring tools will be provided. Detailed information about the food and beverages consumed, such as cooking methods and brand names (if applicable), will be recorded. Nutrient analysis will be generated using the Nutritionist Pro^TM^ Diet Analysis software (Axxya Systems LLC, USA) and the Malaysian Food Composition Database (MyFCD). Nutrient adequacy will be assessed by comparing the intake to the Malaysian Recommended Nutrient Intakes (RNIs) [50]. Adequate intake will be defined as meeting or exceeding 100% of the RNI for macro- and micronutrients Portion size estimation in dietary assessment has been validated as reliable [51]. As dietary data will be parent-reported, research assistant will verify accuracy by reconfirming food intake during data entry prior to nutrient analysis. Basal metabolic rate (BMR) will also be calculated to identify potential underreporting or overreporting of energy intake.

Anthropometric measurements will be conducted by trained research assistant ([name]), a registered dietitian who completed standardized anthropometric assessment training measurement according to the standardized guideline by ISAK [52]. Observer and assessor training will be provided to research staff while obtaining data on 3-days dietary recall, with peer review and error checks to ensure data reliability.

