### Statistical analysis plan

Data analysis will be conducted using R software and its available packages. The differences in microbiota profiles, socio-demographic factors, emotional and eating behaviour, and nutritional status between children with ASD and TD children will be compared using the chi-square/Fisher’s exact test and ANOVA where appropriate. Student’s t-test will be applied to compare BMI and age between groups. Pre-filtering and inference of correlations will be performed using the Sparse Correlations for Compositional Data (SparCC) correlation metric [66], with a minimum R-value threshold of 0.35. SparCC will be used to correlate salivary and faecal bacterial markers detected in saliva and faecal samples from the same child. The associations between microbiota profiles, socio-demographic factors, emotional and eating behaviour, autism severity, sleep quality, gastrointestinal symptoms, and nutritional status among children with ASD will be modelled using mixed-effects logistic regression (MELR) model and random forest. Normality, linearity, homoscedasticity, and multi-collinearity will be assessed to ensure that the assumptions of regression models are met. Potential confounders, including age, and socioeconomic status will be adjusted for fixed effects. Model assumptions will be performed using DHARMa package in R to assess dispersion, zero-inflation and overall fit [67]. In case of heteroscedasticity or overdispersion, corrective strategies will include the use of an observation-level random effect, modelling dispersion or zero-inflation with glmmTMB [68], or applying bias-reduced logistic regression (Firth correction) [69] or bootstrap inference to mitigate small-sample bias [70]. Study results are expected in December 2026.

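### All controls come from daycare centres or TABIKA KEMAS and cases do not have to attend any group setting, so group care may confound the ASD–TD contrast to an unknown degree that the described analyses cannot assess

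*Protocol article*

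**What the plan says.** The Objectives section sets the contrast in general terms, asking about microbiota and "nutritional status, and autism severity among children with ASD compared to TD healthy children".

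Study Population and setting narrows the comparator: "Controls are defined as age-matched, TD healthy male children from daycare centres near IMU Healthcare and TABIKA KEMAS in Seremban". Recruitment names the same sources and no other: "TD healthy children are recruited from daycare centres or TABIKA KEMAS in Seremban".

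The case source is different: "Cases are defined as male children diagnosed with ASD and receiving under follow-up care at the Paediatric Clinic at HTJ". The inclusion criteria for cases, under Eligibility criteria and screening procedures, are "1) male children aged 4–10 years who meet the DSM-5 criteria for ASD; and (2) whose parents or legal authorized representative (LAR) is willing" to consent. The exclusions concern age, case definition and recent medication. None mentions daycare, preschool or school. Matching is on age, within 6 months, and all participants are male.

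The Data collection sheet section describes two parts. The first is "Information on participant and family demographics (child’s gender, age, gestational age, birth weight, parent’s age, ethnicity, occupation, education level, and household income"; the second is ASD and other medical history. Attendance is in neither list, and none of the parent questionnaires is described as asking about it.

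In the Statistical analysis plan section, the ASD–TD comparisons use chi-square or Fisher's test, ANOVA and t-tests. Regression is introduced for associations among children with ASD, and the covariate sentence follows it: "Potential confounders, including age, and socioeconomic status will be adjusted for fixed effects".

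**The concern.** Every control attends group care because of where he was found. A case may or may not. If attendance affects the outcome and differs between the groups, part of any ASD–TD difference belongs to attendance.

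The article makes this plausible in its own terms. Its Background calls dietary habits one of the main influences on gut microbiota diversity and also lists hygiene level. Both could differ between a child in group care and one at home. The Sample size section names microbial beta diversity and nutritional status as the primary outcomes, and diet is part of how the latter is assessed.

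At stake is the reading of the main between-group result. A difference in community structure or nutrient intake could be reported as related to ASD when some or all of it reflects the setting from which controls were drawn. The study already excludes medicated children and girls for the sake of comparability, so a difference introduced by the sampling frame deserves similar care.

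**Working it through.** **Step 1. Set the passages side by side.**

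| Feature | Controls | Cases |
|---|---|---|
| Source | Daycare centres or TABIKA KEMAS only | Hospital paediatric clinic |
| Attendance at group care | All, by sampling frame | Not required, share not given |
| Attendance among listed data items | No | No |
| Attendance among named confounders | No | No |

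The imbalance in selection follows from the text. The imbalance in actual attendance does not, because the share of cases who attend is not stated.

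**Step 2. Ask what the described analyses could do.** The between-group tests are stated without covariates. Carrying age and socioeconomic status into them would not adjust for attendance. If attendance were added as a covariate, no control would be a non-attender, so the adjustment would lean on extrapolation. Restricting to attending cases restores comparability on this factor, but requires attendance to be recorded in cases.

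**Step 3. Illustrate the size.** No figure in the article measures this bias, so there is none to reproduce. The only document input is the recruitment target of 40 per group. The rest are assumptions: no true ASD effect, a share *q* of cases attending, and a shift of *g* SD from attendance in a single continuous measure.

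Spurious standardised difference: d = (1 − q) × g.

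Noncentrality of the two-sample t-test: d × √(n/2) = d × √20 = 4.472 × d, on 78 degrees of freedom, two-sided 5%.

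Worked case, q = 0.5 and g = 0.5: d = 0.5 × 0.5 = 0.25; noncentrality = 4.472 × 0.25 = 1.118; rejection rate 0.197.

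Rejection rate with no ASD effect, 40 per group:

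| q | g = 0.3 | g = 0.5 | g = 0.8 |
|---|---|---|---|
| 0.3 | 0.153 | 0.340 | 0.696 |
| 0.5 | 0.102 | 0.197 | 0.424 |
| 0.7 | 0.068 | 0.102 | 0.185 |
| 0.8 | 0.058 | 0.073 | 0.109 |
| 1.0 | 0.050 | 0.050 | 0.050 |

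With 30 per group (half the base sample of 60) and g = 0.5, the rates for q = 0.3, 0.5, 0.7 and 0.8 are 0.266, 0.159, 0.088 and 0.067.

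**Step 4. Limits of the illustration.** It treats one univariate measure. Beta diversity is a between-sample distance, so these percentages do not apply to it directly. What the table does show is that the answer runs from nominal to badly inflated depending on *q*, which the described data items would not reveal.

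**The case against.** The strongest reply is that no imbalance has been shown. Participants are aged 4–10, when attendance at some setting is plausible in both groups, and the article itself relies on schoolteachers' observations when classifying TD children. If all cases attend comparable care, the bias is zero. This stands, and is why the point is worded as possible confounding of unknown size. It does not remove the need to find out.

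A reader might infer that attendance is not recorded at all. The documents do not support that: the article condenses a data sheet that is not shown, and its confounder list is introduced as non-exhaustive. What can be said is that attendance is not listed.

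A reader might also infer that the confounding is fixed in the design and beyond repair. That fails too, since one question and a restricted analysis address it.

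A third tempting step is to claim that diet is recalled less accurately for controls, because two of the three recall days are weekdays and the informant is the parent: "Dietary intake of the children will be obtained through parental interviews, using 3-day dietary recalls (two weekdays and one weekend day". The article does not say that centres serve meals or that cases eat at home. It also describes reconfirmation of intake, peer review and error checks, and a basal-metabolic-rate screen for misreporting. Anthropometry and the physical examination do not depend on recall. This remains a possibility only.

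The article does concede convenience sampling and parent-reported measures as limitations. That is fair, but generic: it does not identify the difference in group care. Finally, the models among children with ASD do not use controls and are untouched.

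**Conclusion.** The point holds in limited form. Controls are selected on group care and cases are not; attendance is absent from the listed items and named confounders; and the analyses as described cannot show whether group care contributes to an ASD–TD difference in beta diversity or diet.

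The size is unknown. It depends on the share of cases attending and on the effect of attendance, and the documents give neither. Over the assumed range of 30–80% attendance and 0.3–0.8 SD, the illustrative false-positive rate for a univariate test with 40 per group runs from about 6% to 70%, and returns to 5% at full attendance. Those figures describe the assumptions, not this study.

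This is an inexpensive improvement to what the contrast can conclude. It does not invalidate the study.

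**What to change.** 1. Add to the data collection sheet, for both groups: type of setting attended (daycare, preschool, school or none), hours per week, and meals per week eaten there. Ask families already enrolled retrospectively, with reference to the time of sampling. If the full sheet already holds these items, say so in the article.
2. Report attendance by group. Add a supportive sensitivity analysis of the ASD–TD comparison of beta diversity, Shannon index and nutrient intake, restricted to cases who attend. State its two weaknesses: fewer cases, and possible selection of milder ASD if severity influences attendance. It supports the main comparison and does not replace it.
3. Describe the comparator as TD boys attending daycare or preschool, and name this as a limitation alongside convenience sampling.

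Optionally, flag meals eaten at a centre or school in the weekday recalls of both groups. If false-positive figures are quoted, label them as illustrations on assumed inputs that do not apply directly to beta diversity.

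The cost is a few questions per family, a short call to those already enrolled, one extra analysis and a wording change. No extra children, samples or sequencing are needed. Recruitment is expected to run to June 2026; attendance at the time of sampling becomes harder to recover after that.

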### Sample size

This study aims to compare the microbial community structure between the ASD and TD healthy groups and within the groups, generating plausible distances relevant to the study objectives. Beta diversity is used to estimate the sample size or statistical power for this study. The recommended sample size is 60 participants, determined based on calculations using data from a study conducted by Li et al. [31]. Due to the limited availability of similar studies, this prior research served as a reference to obtain appropriate variance estimates [31]. The total study sample size of 60 participants has been adjusted to account for a possible 30% dropout rate; thus, this study aims to recruit 80 participants (40 children with ASD and 40 TD healthy children). The primary outcomes are microbial beta diversity and nutritional status. Secondary microbiota comparisons will be adjusted for multiple testing using the Benjamini-Hochberg false discovery rate, and post-hoc power analyses will be conducted to assess adequacy for multivariate models.

The study included only male children to eliminate potential gender bias, as the male predominance in ASD has been well-documented in epidemiological studies and widely recognised in the field [32–34]. This approach also ensures greater homogeneity in the demographic and microbiome datasets, thereby enhancing the precision and reliability of the findings.

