**Methods and analysis:**

This observational, age-matched, case-control study is conducted in Malaysia among 40 male children with ASD and age-matched with 40 TD healthy controls aged 4–10 years. The dependent variables include the microbiota profile, identified through metagenomic sequencing analysis of saliva and faecal samples, and autism severity, assessed through validated questionnaires. Independent variables include nutritional status, determined through Subjective Global Nutrition Assessment (SGNA), anthropometry and dietary measurements, gastrointestinal symptoms, eating behaviour, behavioural profile, and sleep quality. Data collection is expected to be completed by June 2026. The study nature may limit causality establishment. Analyses will use chi-square/ANOVA for group comparisons, SparCC for microbiota correlations, and mixed-effects logistic regression to model associations.

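### 80 recruits do not cover the stated 30% dropout: that loss leaves 56 children, against the 60 required, and 80 covers a loss of at most 25%

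*Protocol article*

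**What the plan says.** The Sample size section names the measure behind the calculation: "Beta diversity is used to estimate the sample size or statistical power for this study". It then gives the result: "The recommended sample size is 60 participants, determined based on calculations using data from a study" that served as the reference for the variance. The next step is the allowance for loss. The 60 was "adjusted to account for a possible 30% dropout rate; thus, this study aims to recruit 80 participants", 40 with ASD and 40 typically developing. The abstract repeats the split: "40 male children with ASD and age-matched with 40 TD healthy controls aged 4–10 years".

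No other section gives a different dropout rate, a different required number, or a rule for replacing children who drop out.

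**The concern.** A dropout allowance has one purpose: the required number should still be there after the planned loss. Here the required number, the rate and the target stand together and are joined as premise and conclusion, so the claim can be checked from the text alone. The target looks too small for the rate. If so, the article tells its readers that the study tolerates a loss which in fact takes it below its own recommended size.

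Some loss is plausible. According to the section on saliva and stool sampling, parents collect two stool samples at home and then contact the team to arrange transport. A child without a stool sample contributes nothing to gut beta diversity, which is a primary outcome.

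**Working it through.** **Inputs** (all from the Sample size section; the abstract confirms the 1:1 split)
- Required number: 60, or 30 per group at 1:1.
- Dropout rate: d = 30%.
- Recruitment target: 80, or 40 per group.

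**Step 1. Try to reproduce the 80.**
- Dividing by the fraction retained: 60 / (1 − 0.30) = 60 / 0.70 = 85.7, rounded up to 86 (43 per group). This does not give 80.
- Multiplying by one plus the rate: 60 × (1 + 0.30) = 78 (39 per group). This is close to 80 and would reach it by rounding up.
- Solving for the rate at which 80 is exact: 1 − 60/80 = 0.25, so d = 25%.

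The usual formula does not return 80 at the stated rate. The multiplicative shortcut comes near it. That shortcut is the likely origin, but this is an inference, because the article shows no formula.

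**Step 2. Apply the stated rate to the stated target.**
- Total: 80 × 0.70 = 56. Shortfall: 60 − 56 = 4.
- Per group: 40 × 0.70 = 28. Shortfall: 30 − 28 = 2.
- Relative shortfall: 4/60 = 6.7%, about 7%.

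**Step 3. Compare across rates.**

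| Dropout | Left from 80 | Recruits needed to keep 60 |
|---|---|---|
| 20% | 64 | 75 |
| 25% | 60 | 80 |
| 30% | 56 | 86 |

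**Step 4. Illustration, under an assumption.** If each child drops out independently with probability 0.30 (the article does not say this), the binomial probability that at least 60 of 80 remain is about 20%. With 86 recruits it is about 57%.

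**The case against.** **Could the 60 already include the allowance?** The sentence is loosely worded, and a reader might take it that way. But the section first gives 60 as the recommended number and then derives 80 from it. If 60 already contained the allowance, nothing would explain the 80. This reading fails.

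**Is the effect small?** Yes, and this objection stands. The 30% is described only as possible. At any loss up to 25% the target is sufficient, and at 30% it misses by 4 children. The article describes no long follow-up. No outcome, analysis or eligibility rule depends on the correction.

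**Are stronger readings tempting?** Three are, and the article does not support them.

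- *Broken pairs.* A reader might infer from "Cases and controls are matched within using an age range of ±6 months" that each lost child also removes its match, so that far fewer than 56 children would be usable. The Statistical analysis plan section names chi-square or Fisher's exact tests, ANOVA and Student's t-test between groups, and adjusts its models for age. It states no paired or conditional analysis, and no rule drops a child whose match is lost. The 60 is a count of participants. Under the tests as stated, all 56 children stay in, so a count of intact pairs has no part in this point.
- *A definite loss of power.* A reader might convert 56 against 60 into a fall in power. That would need a significance level, a target power and an effect size, none of which is given. A simple square-root-of-n approximation may also not carry over to a distance-based measure such as beta diversity.
- *A need to enrol more.* The contradiction can be removed by restating the tolerance. It does not by itself show that 80 is too few.

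**Conclusion.** The statement is wrong as written. A target of 80 with 30% dropout gives 56 evaluable children (28 per group) rather than 60. The target keeps 60 only up to 25% dropout, and 86 would be needed at 30%. This rests only on the article's own three figures, read as the number before the allowance, the rate, and the number after it. It needs no assumption about the test, the effect size or the pattern of loss; the 20% and 57% probabilities do assume independent dropout and are illustrations only.

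The error is modest: 4 children, about 7% of the required number, and only if the full 30% loss occurs. It is a clear arithmetic error in the sample-size justification and should be corrected, but it does not undermine the study.

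**What to change.** Replace the sentence on the dropout adjustment with one of these:
- *80 recruits provide 60 evaluable children with up to 25% dropout*; or
- *with 30% dropout, 80 recruits leave 56 evaluable children (28 per group)*.

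Either costs one sentence and needs no extra enrolment. The only price is that the stated tolerance for loss becomes slightly less favourable. If the sponsor prefers to keep both the 60 and the 30%, the target that matches them is 86 (43 per group), 6 more children than planned.

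### Post-hoc power is the only sample-size check named for the multivariate models; computed at the observed effect, it follows from the p-value and cannot show adequacy

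*Protocol article*

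**What the plan says.** The Sample size section rests the calculation on one quantity: "Beta diversity is used to estimate the sample size or statistical power for this study". From this it reports that "The recommended sample size is 60 participants", with variances taken from one earlier study ("this prior research served as a reference to obtain appropriate variance estimates"). The total is then "adjusted to account for a possible 30% dropout rate", so that "this study aims to recruit 80 participants (40 children with ASD and 40 TD healthy children").

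For the multivariate models the section gives no prospective power or precision. It says instead that "post-hoc power analyses will be conducted to assess adequacy for multivariate models". It does not state the effect size to be used, the significance level, or the power that would count as adequate.

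The Statistical analysis plan section describes the models. Associations "among children with ASD will be modelled using mixed-effects logistic regression (MELR) model and random forest", with age and socioeconomic status adjusted for as fixed effects. The section also plans checks of regression assumptions and DHARMa diagnostics. Firth correction or the bootstrap is held in reserve for heteroscedasticity or overdispersion. Post-hoc power is not mentioned again.

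**The concern.** The clause names both a method and its purpose, and in its usual meaning the method cannot serve the purpose. Whether a sample is adequate depends on how precisely it estimates the coefficients. Power evaluated at the estimate just obtained depends on the p-value and adds nothing to it.

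The models concerned are fitted in at most 40 children, and the study was not sized for them. Many associations will probably be non-significant. The reader then needs to know which of them exclude an effect of interest and which are merely imprecise. Observed power puts both kinds in the same class, because it is low for every non-significant result.

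**Working it through.** **The plan's own figure.** The article gives no power figure for the multivariate models, so there is nothing to reproduce. The 60 participants cannot be recomputed either, because the article states no effect size, variance, significance level or power. The full protocol may hold these, and their absence is not the point here.

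**Inputs**
- Children with ASD: 40 recruited, or 40 × (1 − 0.30) = 28 after the stated dropout (Sample size).
- Significance level: two-sided 5%. *Assumption; none is stated.*
- Target power: 80%. *Assumption.*
- Outcome prevalence 50% to 20%, and squared multiple correlation of the predictor with the covariates (R²) 0 to 0.3. *Assumptions, shown as a range.*

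**Step 1: observed power as a function of p.** Let z_p be the normal quantile at 1 − p/2. Power at the observed effect is

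Φ(z_p − 1.96) + Φ(−z_p − 1.96).

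The p-value is the only quantity that varies.

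| p | observed power |
|---|---|
| 0.001 | 91% |
| 0.01 | 73% |
| 0.05 | 50% |
| 0.10 | 38% |
| 0.20 | 25% |
| 0.50 | 10% |

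**Step 2: does sample size enter?** For a two-group comparison with n per group and standard deviation 1, the observed difference that gives a chosen p is d = z_p·√(2/n). At p = 0.05, d is 0.524, 0.506 and 0.438 for n = 28, 30 and 40, and observed power is 0.500 each time. At p = 0.20, d is 0.343, 0.331 and 0.287, and observed power is 0.249 each time. Once p is known, n makes no difference.

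**Step 3: where does observed power reach 80%?** This requires z_p = 1.96 + 0.84 = 2.80, which is p of about 0.005. Significant results with p between about 0.005 and 0.05 therefore show between 50% and 80%.

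**Step 4: what can be stated before analysis.** For one predictor in a logistic model,

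log odds ratio per SD = (1.96 + 0.84) / √[n·π(1 − π)(1 − R²)],

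where π is the outcome prevalence.

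| n | π = 0.5, R² = 0 | π = 0.2, R² = 0.3 |
|---|---|---|
| 40 | exp(2.80/√10.0) = 2.43 | exp(2.80/√4.48) = 3.76 |
| 28 | exp(2.80/√7.0) = 2.88 | exp(2.80/√3.136) = 4.86 |

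The expected number of children with the outcome is 20 to 8 at n = 40 and 14 to about 6 at n = 28. These are large-sample approximations for ordinary logistic regression and make no allowance for random effects. They need no outcome data and do not depend on any p-value.

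**Step 5: other checks in the plan.** The assumption checks and DHARMa diagnostics concern whether the model fits. Firth correction and the bootstrap concern small-sample bias. The control of multiplicity ("Secondary microbiota comparisons will be adjusted for multiple testing using the Benjamini-Hochberg false discovery rate") concerns false positives. None of these says what size of association the sample can detect or exclude.

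**The case against.** The strongest reply is that the article does not say the observed effect will be used. Power calculated after recruitment, at the achieved n and for an effect fixed in advance, does not restate p, and a condensed article may leave that choice to a fuller document. This is a possible reading, so the conclusion must be conditional on the usual meaning of the term. It does not rescue the clause as it stands: neither section names such an effect, and if one is intended, the calculation can be done now.

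A reader might also infer three stronger things that the document does not support.

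- *Significant associations will be certified as adequately powered.* The arithmetic contradicts this. At p = 0.01 observed power is 73%, below the usual 80%. The article also sets no threshold or decision rule, so how the results would be labelled is not known.
- *The multivariate models have no other check at all.* They do have checks, on fit and on small-sample bias. Post-hoc power is the only **sample-size** check named.
- *Detectable correlations are the right replacement.* They do not fit the logistic and random forest models that are planned.

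It is also fair to say that the clause governs neither the sample size nor a primary test.

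**Conclusion.** The point holds in a limited form. If post-hoc power means power at the observed effect, and the level is two-sided 5%, it cannot show whether the sample was adequate for the multivariate models. The equivalence with p is exact for a single-coefficient z or Wald test and approximate for other tests. Every non-significant association will show about 50% power or less, whatever its confidence interval excludes. For random forest, power of this kind has no direct meaning.

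The severity is minor. The clause affects the interpretation of the association models among children with ASD and leaves the primary beta-diversity comparison untouched.

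**What to change.** 1. Delete the post-hoc power clause from the Sample size section.
2. Say that adequacy of the logistic models will be judged by the 95% confidence intervals of their coefficients.
3. State before analysis the effect detectable with 80% power in the within-ASD logistic models, with the assumptions shown. For example: an odds ratio per SD of one predictor of about 2.4 to 3.8 with 40 children and 2.9 to 4.9 with 28, for outcome prevalence 50% to 20% and R² with covariates 0 to 0.3. The study team should replace these ranges with its own values.
4. For random forest, report cross-validated or out-of-bag performance with its uncertainty.

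The cost is a few sentences and no extra data. The downside is that the stated detectable effects will look unfavourable.
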